### Outcomes

The main outcome is loss of kidney function, defined as urine volume output less than 100 mL in 24 h, 12 months after the initiation of haemodialysis therapy.

The secondary outcomes are: (1) erythropoietin dosage, (2) beta-2 microglobulin concentration, (3) hydration and nutritional status, (4) concentrations of uremic toxins, (5) dialysis dose, (6) number and duration of hospital admissions, (7) mortality and (8) quality of life.

In addition, cost-efficiency will be assessed by recording the cost of haemodialysis sessions and the monthly consumption of erythropoietin.

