### Trial design

This is a randomized prospective multi-centre open-label clinical trial. Randomization will be stratified in every recruitment centre, ensuring a 1:1 ratio between the two study groups in all centres. The trial compares the initiation of renal replacement therapy with two haemodialysis sessions per week to the conventional three sessions per week in patients with residual urea clearance rate KrU ≥ 2.5 mL/min/1.73 m^2^. As treatment masking is not feasible, treatment allocation is centralized for all participating hospitals, and performed by an agent external to the researchers. Once a participating centre has verified that a patient meets the inclusion criteria, the randomization centre will provide the treatment group allocation. The investigators will not know the randomization sequence. The two groups will be those beginning with two haemodialysis sessions per week (2HD) and those beginning with three haemodialysis sessions per week (3HD).

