### Assessments

The following will be assessed at the momento fo enrollment: age, sex, renal disease, Charlson comorbidity index, urine volume output in 24 h (mL), urea clearance (mL/min), creatinine clearance (mL/min).

The following will be assessed at the start of haemodialysis treatment (baseline) and every 2 months during a follow-up of at least 1 year: urine volume output in 24 h (mL), urea clearance (mL/min), creatinine clearance (mL/min), haemoglobin (g/dL), haematocrit (%), creatinine (mg/dL), urea (mg/dL), Na (mmol/L), K (mmol/L), albumin (g/dL), pre-albumin (mg/dL), calcium (mg/dL), phosphorus (mg/dL), parathyroid hormone (pg/mL), ferritin (ng/mL), beta-2 microglobulin (mg/L), brain-derived natriuretic peptide (pg/mL), C-reactive protein (mg/L), dose of dialysis (*Kt / V*), erythropoietin dosage (units per week per kg of weight), hydration, nutrition, hospital admissions, days of admission, causes of hospitalization and number of haemodialysis sessions.

The dose of dialysis is determined using the kinetic model of urea with the formulae modified from Gotch [22]. Dialysis *Kt* / *V* [3] is added to the residual renal function to give the total *Kt* / *V*:

Total *Kt* / *V* = dialysis *Kt* / *V* + (9.5 KrU) / *V* (for 2 haemodialysis sessions per week)

and

Total *Kt* / *V* = dialysis *Kt* / *V* + (5.5 KrU) / *V* (for 3 haemodialysis sessions per week),

where *V* is 58% of the dry weight (Watson formula) [23] and KrU is the residual urea clearance rate (mL/min).

Hydration and nutrition are measured by multi-frequency electrical bioimpedance (BCM®, Fresenius Medical Care). The following metrics are collected: overhydration (L), amount of extracellular water (L), amount of intracellular water (L), extracellular / intracellular ratio, body mass index (kg/m^2^), lean tissue index (kg/m^2^) and fat tissue index (kg/m^2^).

Quality of life will be assessed using the Kidney Disease Quality of Life Short Form at the start of haemodialysis treatment (baseline), at 6 months and at 12 months (close-out). This is a validated questionnaire for the haemodialysis population.

The schedule of enrolment, intervention and assessments is shown in Fig. 1.

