### Criteria for progression

The dialysis technique used for each patient (high-flow haemodialysis or haemodiafiltration online) will be maintained throughout the follow-up period. The 3HD group will start with three sessions lasting 3–3.5 h to achieve an adequate dialysis *Kt* / *V*. The 2HD group will start with two sessions of 4 h.

According to Casino and López [24], to obtain an equivalent renal urea clearance rate of 11 mL/min, the adequate dialysis *Kt* / *V* should be 1.6 or 1.2 for 2 sessions per week and 3 sessions per week, respectively. Modifications to the dialysis procedure, such as increasing the blood flow, bath flow, dialyzer surface or duration of the dialysis session, will be made if patients do not reach an adequate *Kt* / *V*.

Participants in the 2HD group will be switched to the 3HD group if their urea clearance rate falls below 2.5 mL/min/1.73 m^2^ in two determinations made in a 2-week interval, or they develop uncontrolled hypertension, heart failure, or a clinical event that indicates that the number of haemodialysis sessions should be increased.

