## Discussion

The transition from pre-dialysis to renal replacement therapy is a crucial moment for patients with chronic renal failure and has significant clinical, social and occupational impacts [27]. Although dialysis therapy may predispose someone to losing their residual renal function, a significant proportion of dialysis patients maintain some degree of renal function long after the initiation of dialysis. In addition, maintaining the residual function may have a positive impact on the survival of haemodialysis patients [8, 12–15].

An incremental approach to the initiation of dialysis may allow some patients to retain more of their residual renal function with an improved quality of life and similar or higher survival rates than those receiving the conventional treatment, as reported by observational studies [4–7, 12, 16, 18, 19, 28]. We also consider that the incremental schedule facilitates the transition to renal replacement therapy and additionally, contributes to reducing health-care costs, not only because there are fewer haemodialysis sessions but also a lower consumption of erythropoietin [4, 7].

However, all previous studies have been observational, and prospective trials, such as this one, are required to determine, without selection bias, the potential benefits and safety of the incremental schedule [9–11, 28], and to establish the optimal group of patients who would benefit from this therapy.

This randomized clinical trial compares twice- versus thrice-weekly haemodialysis sessions for patients who can maintain a residual urea clearance rate KrU ≥ 2.5 mL/min/1.73 m^2^, without excluding a priori patients with severe comorbidities. In our experience, more than 80% of patients who started incremental renal replacement treatment did not suffer from any relevant complications [17]. For these patients, the dose of dialysis was progressively adjusted as their residual renal function declined. In our protocol, diuresis in 24 h is used as a proxy of residual renal function. The transition to more frequent treatment sessions occurs once residual renal function starts to decrease. However, it is essential to determine whether incremental haemodialysis is a safe form of dialysis treatment.

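### The cost-efficiency assessment names dialysis sessions and erythropoietin as its cost items and leaves hospital admissions uncosted, so it could misstate the overall cost difference in either direction

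*Protocol article*

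**What the plan says.** After the eight secondary outcomes, the Outcomes section adds that "cost-efficiency will be assessed by recording the cost of haemodialysis sessions and the monthly consumption of erythropoietin". The same section lists, as a separate secondary outcome, "6) number and duration of hospital admissions". The Assessments section schedules, at baseline and every 2 months, the recording of "hospital admissions, days of admission, causes of hospitalization and number of haemodialysis sessions". No sentence ties the admission data to cost.

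The arms are defined under Trial design as "those beginning with two haemodialysis sessions per week (2HD) and those beginning with three haemodialysis sessions per week (3HD"). Criteria for progression sets the starting session lengths: "The 3HD group will start with three sessions lasting 3–3.5 h", and "The 2HD group will start with two sessions of 4 h". It also gives the one planned change of frequency: "Participants in the 2HD group will be switched to the 3HD group if their urea clearance rate falls below 2.5 mL/min/1.73 m^2", or for certain clinical events. No rule moves a 3HD patient to fewer sessions.

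The Discussion states the expectation that the incremental schedule "contributes to reducing health-care costs, not only because there are fewer haemodialysis sessions but also a lower consumption of erythropoietin". The Background also expects lower erythropoietin doses. In addition, it cites a lower rate of admissions with incremental dialysis and reports a favourable effect on hospitalization in the coordinating unit's own experience.

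**The concern.** Of the two cost items named, one is the randomised intervention itself and the other is an item on which the article already expects a saving. They are the same two items that the Discussion gives as the reasons for lower cost. Hospital stays, a third and potentially large item, are measured in every patient but do not enter the cost.

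The article names its cost inputs, so this is a choice that can be reviewed and not merely a detail left for later. The set is narrow for something called cost-efficiency. A cost difference computed as written describes dialysis and erythropoietin spending. If it is read as the overall cost difference, it will be wrong by whatever the arms differ in hospital cost. That error could enlarge, shrink or reverse the apparent saving. The events that trigger progression include cardiac failure and uncontrolled blood pressure, which could plausibly lead to admission. The article's own expectation, however, runs towards fewer admissions with 2HD.

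**Working it through.** The article gives no cost figure, so there is no stated result to reproduce. What can be checked is how far allocation fixes the session item, and how large an admission difference would have to be to matter.

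**Inputs from the article.** Sessions per week at the start: 2 versus 3 (Trial design). Session length at the start: 4 h versus 3–3.5 h (Criteria for progression). Follow-up: at least 1 year (Participants).

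**Assumptions, not in the article.**
- *f* is the mean share of the first year that 2HD patients spend on three sessions after switching. It is varied from 0 to 1.
- *k* is the cost of one hospital day expressed in sessions. It is varied from 1 to 5.
- A session costs the same in both arms, erythropoietin is equal, and there are no unscheduled sessions.

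**Step 1: sessions per patient-year.**
- 3HD: 3 × 52 = 156.
- 2HD: 52 × [2(1 − f) + 3f] = 52 × (2 + f).
- Difference: 52 × (1 − f).

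| f | 2HD | 3HD | Fewer in 2HD | % |
|---|---|---|---|---|
| 0 | 104 | 156 | 52 | 33.3 |
| 0.25 | 117 | 156 | 39 | 25.0 |
| 0.5 | 130 | 156 | 26 | 16.7 |
| 0.75 | 143 | 156 | 13 | 8.3 |
| 1 | 156 | 156 | 0 | 0 |

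Switching can bring the difference down to zero. It cannot reverse it unless there are unplanned extra sessions.

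**Step 2: dialysis hours per week at the start**, in case cost follows time more than count.
- 2HD: 2 × 4 = 8 h.
- 3HD: 3 × 3 = 9 h to 3 × 3.5 = 10.5 h.
- Reduction: 1 − 8/9 = 11% to 1 − 8/10.5 = 24%.

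The direction is the same, but the difference is smaller than the 33% by count.

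**Step 3: admission days that would cancel the session saving**, per patient-year: 52 × (1 − f) / k.

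| f | k = 1 | k = 2 | k = 3 | k = 5 |
|---|---|---|---|---|
| 0 | 52 | 26 | 17.3 | 10.4 |
| 0.25 | 39 | 19.5 | 13 | 7.8 |
| 0.5 | 26 | 13 | 8.7 | 5.2 |
| 0.75 | 13 | 6.5 | 4.3 | 2.6 |

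The table reads both ways. That many extra days in 2HD would erase the saving; the same number fewer would double it. Neither would show in the cost result as the article describes it.

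**The case against.** The strongest reply has five parts.

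- **The sentence concerns data capture in a condensed article.** It does not say that admissions will never be costed, and unit costs or an effect measure may sit in a fuller document. This stands for the effect measure: its absence here is no finding. It does not remove the point about cost items, because the article names two and no others.
- **Any harm would be visible.** Admissions and mortality are secondary outcomes and would be reported beside the cost figure. This is correct, and it limits the damage. It does not make the cost figure complete.
- **The article expects fewer admissions with 2HD.** On that expectation, leaving them out works against 2HD. This stands, and it is why the error has no known direction.
- **The size of the saving is not fixed.** It depends on how soon patients switch, on erythropoietin use and on cost per session, which may differ because 2HD sessions are longer and the procedure may be modified. This stands too.
- **The offset is hypothetical.** It rests on assumed values of *f* and *k*, and nothing in the article points to an excess of admissions of that size. This is also right; the table shows sensitivity and is not a forecast.

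A reader might infer that the result is settled in advance in favour of 2HD, or that the plan hides a harm. The article does not support either reading. Allocation fixes only the direction of the session item. Erythropoietin is measured and not assigned, and admissions are openly reported.

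**Conclusion.** The point holds in a limited form. The cost items named for cost-efficiency are sessions, which allocation makes lower in 2HD, and erythropoietin, which the article expects to be lower. The session difference is at most 52 per patient-year (33%), or 11–24% by starting hours, and it shrinks towards zero with early switching. Hospital admissions, already recorded, are not costed, so the result could misstate the overall cost difference in either direction. The size of that error cannot be computed from the article because it gives no unit costs. Under the assumed range of 1 to 5 sessions per hospital day, a between-arm difference of about 10 to 52 days per patient-year matches the full session saving, and about 5 to 26 days matches it if half the year is spent on three sessions.

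Cost-efficiency is an additional assessment. It does not enter the hypothesis or the sample size, and the primary result is unaffected.

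**What to change.** In Outcomes, define cost per patient, by allocated arm over the first 12 months, as the sum of:

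- all dialysis sessions actually delivered, including unscheduled ones and those after a switch to three per week;
- erythropoietin;
- days of hospital admission multiplied by a stated unit cost.

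Report the difference between arms with and without the admission component, so that the reader can see what each part contributes. If admissions are not to be costed, the minimum change is to label the result as dialysis and erythropoietin cost only, and to draw no conclusion from it about overall cost.

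The full change costs one sentence and one inpatient-day unit cost. Sessions, erythropoietin, admissions and days are already in the Assessments list, so no new patient data are needed. The downside is precision: admission days vary widely between patients, and with the planned 44 per group the interval around the total cost difference will be wider than for dialysis and erythropoietin alone. Showing both versions keeps the narrower comparison available.

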### Trial design

This is a randomized prospective multi-centre open-label clinical trial. Randomization will be stratified in every recruitment centre, ensuring a 1:1 ratio between the two study groups in all centres. The trial compares the initiation of renal replacement therapy with two haemodialysis sessions per week to the conventional three sessions per week in patients with residual urea clearance rate KrU ≥ 2.5 mL/min/1.73 m^2^. As treatment masking is not feasible, treatment allocation is centralized for all participating hospitals, and performed by an agent external to the researchers. Once a participating centre has verified that a patient meets the inclusion criteria, the randomization centre will provide the treatment group allocation. The investigators will not know the randomization sequence. The two groups will be those beginning with two haemodialysis sessions per week (2HD) and those beginning with three haemodialysis sessions per week (3HD).

### Participants

The participants are incident patients at five university hospitals in the Community of Madrid (Spain): H. U. Ramón y Cajal (coordinating centre), H. U. del Henares, H. U. La Paz, H. U. Príncipe de Asturias and H. U. Clínico San Carlos. The minimum follow-up period will be 1 year.

#### Inclusion criteria

Prospective participants must have stage 5 chronic kidney disease, must have started chronic haemodialysis and must be able to maintain a residual urea clearance rate KrU ≥ 2.5 mL/min/1.73 m^2^. Before enrolment, participants must sign the informed consent form.

#### Exclusion criteria

Anuric patients, patients with acute renal failure, and patients who return to haemodialysis after a kidney transplant failure will be excluded from the trial.

### Withdrawal criteria

Patients will be withdrawn from the study if they receive a renal transplant, die***,*** recover renal function or transfer to another facility or if they withdraw their informed consent.

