**Methods/design:**

This report describes the study protocol of a randomized prospective multi-centre open-label clinical trial to evaluate whether starting renal replacement therapy with twice-weekly haemodialysis sessions preserves residual renal function better than the standard thrice-weekly regimen. We also explore other clinical parameters, such as concentrations of uremic toxins, dialysis doses, control of anaemia, removal of medium-weight uremic toxins, nutritional status, quality of life, hospital admissions and mortality. Only incident haemodialysis patients who can maintain a urea clearance rate KrU ≥ 2.5 mL/min/1.73 m^2^ are eligible. Patient recruitment began on 1 January 2017 and will last for 2 years or until the required sample size has been recruited to ensure the established statistical power has been reached. The minimum follow-up period will be 1 year. Anuric patients with acute renal failure and patients who return to haemodialysis after a kidney transplant failure are excluded. It has been calculated that 44 patients should be recruited into each group to achieve a power of 80% in a two-sided comparison of means with a usual significance level of 0.05. A time-to-event analysis will estimate the probability of kidney function survival in both groups using the Kaplan–Meier method. Survival curves will be compared with log-rank tests. This survival analysis will be complemented with a proportional hazard model to estimate the hazard ratio of kidney function survival adjusted for any confounding factors. Analyses will be carried out in accordance with the intention-to-treat principle.

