## Methods/design

### Hypothesis

Our hypothesis is that initiating renal replacement therapy with twice-weekly haemodialysis sessions preserves residual renal function better than the conventional regimen of beginning with thrice-weekly sessions. In addition, we hypothesise that maintaining renal function provides beneficial clinical effects, such as better control of anaemia, greater removal of medium-weight uremic toxins, and better nutritional status and quality of life, and has a safety profile like that of the conventional schedule.

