### Data collection and statistical analysis

The data collected will be stored in a database specially designed for this study using Access (Microsoft Office Access 2007). The data will be entered by a dedicated member of the project team, who will ensure the integrity and quality of the data. The statistical analyses will be carried out with the statistics program Stata v.14 [25].

We will perform a blind interim analysis when at least half of the patients have been recruited and followed for at least 1 year. We will stop the trial if the group difference in the main outcome is statistically significant at a significance boundary *p* < 0.0051. The final analysis with the whole trial population will be carried out at the end of the follow-up at a significance level of 0.04795.

For the univariate analysis of quantitative variables, we will check the normality of the data using the Kolmogorov–Smirnov test. Depending on the assumption of normality, the two arms will be compared using parametric tests (Student’s *t*-test) or nonparametric tests (Mann–Whitney *U* test). The associations of categorical variables with the two treatment groups will be assessed by chi-squared tests or Fisher exact tests, as appropriate.

The loss of renal function is evaluated by the diuresis in 24 h at 12 months after initiation of haemodialysis therapy, and it is dichotomized with a threshold of 100 mL in 24 h. A time-to-event analysis will estimate the probability of loss of kidney function in both treatment groups using the Kaplan–Meier method. Survival curves will be compared with log-rank tests. This survival analysis will be complemented with a proportional hazard model to estimate the hazard ratio of kidney function survival adjusted for any confounding factors to identify any imbalance in the baseline characteristics of the patients.

All analyses will be carried out in accordance with the intention-to-treat and per-protocol principles, assuming that in the worst case the losses to follow-up are a failure of the allocated treatment arm. In the final analyses, for the comparisons between the two treatment groups, the probability of rejecting the null hypothesis will be adjusted according to the O’Brien and Fleming method [26].

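### Transplant, recovery of function or transfer ends study participation, with no provision for recording deaths and admissions afterwards

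*Protocol article*

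**What the plan says.** Withdrawal criteria (protocol article) opens with "Patients will be withdrawn from the study if they receive a renal transplant". The same sentence adds death, and then patients who "recover renal function or transfer to another facility or if they withdraw their informed consent". All five events have one consequence, leaving the study. Stopping the dialysis assessments is not distinguished from stopping follow-up.

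The Outcomes section lists among the secondary outcomes "6) number and duration of hospital admissions, (7) mortality and (8) quality of life". The Hypothesis section expects that the twice-weekly start "has a safety profile like that of the conventional schedule", and the Discussion says that "it is essential to determine whether incremental haemodialysis is a safe form of dialysis treatment". Under Assessments, admissions, days of admission and causes of hospitalisation belong to the two-monthly follow-up, which lasts at least one year.

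On analysis, the abstract says "Analyses will be carried out in accordance with the intention-to-treat principle". Data collection and statistical analysis says "All analyses will be carried out in accordance with the intention-to-treat and per-protocol principles", and continues "assuming that in the worst case the losses to follow-up are a failure of the allocated treatment arm".

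**The concern.** Transplant, recovery and transfer may make the two-monthly dialysis measurements impossible. They do not prevent anyone from finding out whether the patient is alive or has been admitted to hospital. If the withdrawal sentence is applied as written, a death or admission is seen only when it comes before one of these events.

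The events happen after randomisation and need not be unrelated to arm or prognosis. Recovery of function is close to what the twice-weekly start is meant to preserve. Transfer can follow from clinical state or from the session schedule, and the trial is open-label. At stake is the completeness of the mortality and admission data in a trial that puts safety in its hypothesis. With 44 patients per arm, deaths will probably be few, so each one missed counts.

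**Working it through.** **1. The plan's own figure.** The only design figure is 44 per group. Inputs from Sample size: monthly declines of 0.18 and 0.33 mL/min (difference 0.15), SD 0.25, two-sided 0.05, power 80%. n = 2 × (1.96 + 0.8416)² × (0.25/0.15)² = 2 × 7.849 × 2.778 = 43.6, so 44. The figure reproduces and is not disputed here. It contains no allowance for early leavers, and the article gives no withdrawal or death rate.

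**2. The sections side by side.**
- Withdrawal criteria ends participation at transplant, recovery or transfer.
- Outcomes and Hypothesis need deaths and admissions for all randomised patients.
- The analysis section promises intention-to-treat, and treats losses to follow-up in the worst case as failures.
- That rule does not say whether a withdrawn patient is a loss to follow-up. It has no meaning for a number or duration of admissions. Applied to mortality, it would score living transplanted or recovered patients as failures.

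**3. How much follow-up could be lost (assumed rates).** If 10%, 20% or 30% of the 88 patients leave by these routes, that is 8.8, 17.6 or 26.4 patients. If they leave mid-year on average, the loss is 0.5 year each, or 5%, 10% or 15% of the 88 first-year patient-years.

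**4. What this could do to mortality (assumed rates).** Let true 12-month mortality be 10% in both arms (4.4 deaths per arm), w the share withdrawn, and r the risk in leavers relative to stayers. Assume that r is the same in both arms and that all deaths in leavers fall after withdrawal and are missed. Then:
- risk among stayers = 0.10 / (1 − w + w·r)
- observed deaths per randomised patient = (1 − w) × that risk

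| Withdrawn, arm A v arm B | r | Observed per randomised | Among stayers only |
|---|---|---|---|
| 10% v 10% | 1 | 9.0% v 9.0% | 10.0% v 10.0% |
| 10% v 10% | 2 | 8.2% v 8.2% | 9.1% v 9.1% |
| 10% v 20% | 1 | 9.0% v 8.0% | 10.0% v 10.0% |
| 10% v 20% | 2 | 8.2% v 6.7% | 9.1% v 8.3% |
| 5% v 25% | 3 | 8.6% v 5.0% | 9.1% v 6.7% |

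Example, 20% withdrawn and r = 2: 0.10 / (0.80 + 0.40) = 8.33% among stayers, and 0.80 × 8.33% = 6.7% observed.

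Equal withdrawal loses events but creates no difference between arms. A false difference needs unequal withdrawal and, among stayers only, also a different risk in leavers. This conclusion depends on r being the same in both arms. If the kind of patient who leaves differed by arm, equal shares would not protect: 10% withdrawn in each arm with r = 1 v 3 gives 9.0% v 7.5%. Nothing in the article points to such a pattern.

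**The case against.** The strongest reply is that this is a journal article, and what is recorded after withdrawal may stand in the full protocol. Nowhere does the article say that collection of deaths stops. Death itself is on the withdrawal list while mortality is an outcome, so withdrawal cannot mean that data are discarded. Patients contribute until they leave, the analysis is by allocated arm, and a rule for losses is stated. Acute renal failure is excluded, and nothing suggests that recovery is common or that transplant or transfer would differ by arm. Mortality and admissions are secondary, and 44 per arm cannot settle them: even 2 v 7 deaths gives a Fisher p of 0.16, and 4 v 6 gives 0.74.

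Much of this stands. A reader might infer that collection definitely ceases, that the safety comparison rests on a subgroup selected after randomisation, or that it is no longer intention-to-treat. The article supports none of these. Continued collection is simply not provided for, every patient counts up to departure, and truncated follow-up is a missing-data problem within an analysis by allocated arm. Nor are deaths and admissions the only clinical evidence on safety. Hydration, potassium, natriuretic peptide and quality of life are also collected, and uncontrolled hypertension and heart failure are named as reasons to switch schedule.

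The reply does not remove the point. The withdrawal sentence is a stated rule, not a silence, and it treats a transferred patient like one who has withdrawn consent. The rule for losses cannot stand in for vital status that could be obtained. Low power for mortality is no reason to lose events that one enquiry could recover.

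**Conclusion.** The point holds as a weakness in the withdrawal rule that should be corrected. Read as written, follow-up for mortality and admissions ends at transplant, recovery or transfer, which is hard to reconcile with an intention-to-treat analysis of those outcomes. The consequence is lost events and possibly informative censoring, not a demonstrated bias.

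Its size is unknown because the article gives no rates. Under the assumptions shown (10% true mortality in both arms, the same relative risk in leavers in both arms, all their deaths missed), the false difference in mortality per randomised patient runs from none with equal withdrawal to 3.6 percentage points (8.6% v 5.0%) in the most unequal case tabulated. In 44 patients per arm those percentages are 3.8 v 2.2 deaths, so the distortion is one or two deaths. The primary outcome and the sample size are not affected by this point.

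**What to change.** In Withdrawal criteria, distinguish two things: the end of the two-monthly dialysis assessments (transplant, recovery, transfer), and withdrawal from the study (withdrawn consent). For every patient who has not withdrawn consent, record vital status and hospital admissions, with dates and days, to at least 12 months after initiation of haemodialysis. That is the time origin already used in Outcomes and in the analysis section. A record check or one contact with the receiving unit is enough. Analyse these outcomes by randomised arm.

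In Data collection and statistical analysis, limit the worst-case rule to patients whose outcome is truly unknown, and say for each reason for leaving how it is handled for each outcome.

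The cost is a change of wording and one record check or call per early leaver: about 9 to 26 patients if 10% to 30% leave. The consent wording must allow it. No study procedure is added and no treatment changes.
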